#### Secondary outcome analysis

Secondary outcomes will be analysed within the same cluster randomised framework, accounting for clustering at the design level using mixed-effects models or generalised estimating equations as appropriate to the distribution of each outcome. All-cause mortality and hospital visits/hospitalisations, measured as counts or rare events, will be analysed using mixed-effects Poisson or logistic models (or Cox proportional hazards models where individual-level time-to-event data are available), with results reported as IRRs, risk ratios or HRs with 95% CIs. Indoor heat index and UTCI, both continuous environmental exposure measures, will be assessed using linear mixed-effects models with random intercepts for clusters and adjustment for temporal variation to estimate mean differences between trial arms. Thermal comfort, measured either as a continuous score or ordinal response, will be analysed using linear mixed models or ordinal logistic mixed-effects models depending on scale properties. Subgroup analyses will be conducted by including interaction terms between intervention assignment and key effect modifiers such as age (Women of reproductive age, children and elderly), sex and occupational exposure. All models will be adjusted for relevant covariates where appropriate, and robustness will be assessed through sensitivity analyses including alternative correlation structures. Cost-effectiveness analysis will be conducted to evaluate the economic feasibility of different adaptation strategies.

Analysis for subset outcomes measured in the subset of the population will be analysed using multilevel mixed-effects models to account for repeated measurements within individuals and clustering at the household or cluster level, as appropriate. Personalised heat exposure, collected longitudinally, will be analysed as a continuous outcome using linear mixed-effects models incorporating time-varying covariates such as occupation, daily activity patterns and reported illness history. Physiological strain markers obtained from wearable devices (eg, heart rate, sleep metrics and related indices) will be analysed using hierarchical mixed-effects models to estimate intervention effects on both average levels and temporal trajectories over the study period, with additional smoothing or functional approaches considered for high-frequency data. All analyses will report adjusted mean differences with corresponding 95% CIs and will explore heterogeneity in effects over time and across participant characteristics where data permit.

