### Outcomes

All primary, secondary and outcomes assessed for subset of population along with definitions are provided in table 1 and figure 2.

**Table 1 T1:** Outcomes

Primary outcomes	
Heat-related illness	Defined as a documented heat condition/illness according to the International Classification of Disease-11th Revision and institutional classification which classifies heat-related illness as heat stroke, heat syncope, heat exhaustion, heat fatigue, heat cramps and heat rash (figure 2).^30 31^
Quality of life	Quality of life would be assessed according to the WHOQOL-BREF* tool and assessed during two consecutive peak summer and winter seasons.

Secondary outcomes	
Health outcomes	
All-cause mortality	Defined as the total number of deaths in the study population over the study period
Hospital visit/hospitalisation	Defined as the number of hospital admissions (primary, secondary or tertiary facilities) during summers
Environmental outcomes	
Heat Index	Indoor heat index (temperature and humidity)^32^ measured through fixed weather devices
Universal Thermal Climate Index	Defined as a biometeorological index that describes the human body’s physiological response to the environment. It integrates air temperature, humidity, wind speed and radiant temperature to assess the overall thermal stress on the human body
Thermal comfort	Defined as change in the condition of mind that expresses satisfaction with the thermal environment
Outcomes measured for subset of population (individual level)	
Personalised heat exposure	Defined as mean daily external temperature each individual experiences (indoors and outdoors) as recorded by a wearable temperature monitor.
Heart rate	Defined as mean heart rate measurements (beats per minute) taken at 1-hour interval as recorded by wearable android device
Sleep quality	Defined as a biological process that alternates between non-rapid eye movement sleep and rapid eye movement sleep as recorded through a wearable android device
Physical activity	Defined as mean daily duration of sedentary, lightly active, moderately active and very active as measured using a wearable android device.
Energy expenditure	Defined as average total number of calories burned in a day recorded using a wearable android device.
Economic outcomes	
Cost-effectiveness	Measured as the difference in cost divided by the difference in health effect between the intervention and control groups

* WHO Quality of Life Brief tool.

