### Devices

The devices and their utilisation for outcome measurements are provided in table 2.

**Table 2 T2:** Devices used for outcome measures

Outcome measures	Device	Placement
Individual and household level exposure	Thermochron ibuttons, Temp-U which record temperature and humidity	Put at select households in the intervention and control clusters within the main living room, midway between floor and ceiling and away from any direct heat source. Devices will be given to individuals selected for subgroup for individual exposure assessment
Environmental exposure	Kestrel 5400 which will record multiple environmental parameters like wet bulb globe temperature, solar radiation, barometric pressure, wind speed and humidity	One device rotated in each cluster
Individual physiological outcomes	Fitbit Inspire 3 wearable fitness tracker that will track heart rate, sleep cycles, activity levels and energy consumption	Given to the subset population selected in the intervention and control clusters
Weather	Kestrel drop D2 and HOBO U-30 weather stations	One weather station placed at the field office as a central location and one Kestrel drop D2 placed in each cluster

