### Data collection from subset population

Monthly data will be collected from the subset population to provide detailed insights into heat stress and intervention effectiveness (table 3). This will include assessment of thermal comfort, mental health and heat exposure.

**Table 3 T3:** Schedule of outcome assessments and follow-up activities

Parameter	Time points	Details	Devices/tools	Population/unit
Primary outcomes				
All heat-related illness	Weekly during peak summers	Heat-related illnesses	Weekly community survey, health facility data, community surveillance	All members of included households
Quality of life	Mid of April, July and December for two consecutive years	Quality of life mean score	WHOQOL-BREF* questionnaire	Indexed adults of all included households
Secondary outcomes				
All-cause mortality	Weekly during peak summers	Any mortality occurring within the included clusters	Weekly community survey, health facility data, community surveillance	All members of included households
Hospital visit/hospitalisation	Weekly during peak summers	Any hospital admission or hospital visit occurring within the included clusters	Weekly community survey, health facility data, community surveillance	All members of included households
Indoor Heat Index	Continuous throughout the year	Indoor data loggers	Ibutton, Kestrel Drop D2, Temp-U	All included households
Thermal comfort (home)	Monthly	Self-reported comfort levels	Thermal comfort survey adapted from CHEQ-5‡	Indexed adults randomised for subgroup
UTCI	Continuous throughout summers	Outdoor only	Kestrel Drop D2, Kestrel 5400, HOBO weather station	Overall catchment area
Outcomes measured for subset of population				
Personalised heat exposure	Baseline, Monthly	Occupation, sun exposure, illness history, daily routine	Structured survey tool (adapted from HotHaps) and Temp-U	Indexed adults randomised for subgroup
Physiological strain markers	Continuous throughout summers	Heart rate, sleep cycles, VO₂ max†	Fitbit Inspire 3	Indexed adults randomised for subgroup

Participant compliance will be monitored through spot checks and periodic review of device data. For Fitbit devices, heart rate data will be reviewed, as prolonged absence of heart rate recordings may indicate that the device was not worn. Similarly, iButton and Temp-U data will be checked periodically for implausible temperature spikes or sudden drops, which may indicate non-compliance or incorrect device use.

* WHO Quality of Life Brief tool.

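### All-cause mortality, UTCI and hospital use are defined inconsistently between Table 1, Table 3 and the secondary analysis and must be reconciled

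*Protocol article*

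**What the plan says.** All places are in the Protocol article.

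**Mortality.** Table 1 (Outcomes) has all-cause mortality "Defined as the total number of deaths in the study population over the study period". The Study design section runs field activities from 1 January 2026 to 31 December 2027. Table 3 (Schedule of outcome assessments) gives the time points for mortality as "Weekly during peak summers". The survey, facility data and community surveillance all stand on that same row.

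**UTCI.** Under Secondary outcome analysis: "Indoor heat index and UTCI, both continuous environmental exposure measures, will be assessed using linear mixed-effects models", with cluster random intercepts, to estimate mean differences between arms. Table 3 confines UTCI to outdoor measurement, gives its unit as "Overall catchment area" and lists the devices as "Kestrel Drop D2, Kestrel 5400, HOBO weather station". On placement, Table 2 (Devices) has "One weather station placed at the field office as a central location and one Kestrel drop D2 placed in each cluster", with the Kestrel 5400 rotated.

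**Hospital use.** Table 1: "Defined as the number of hospital admissions (primary, secondary or tertiary facilities) during summers". Table 3: "Any hospital admission or hospital visit occurring within the included clusters". The secondary analysis section names visits and hospitalisations together.

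**The concern.** Each of the three outcomes is fixed in two places that cannot both be followed.

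For mortality, a two-year all-cause count and a hot-season count are different estimands. The schedule as written delivers only the second, while the definition promises the first. The analysis section offers Poisson, logistic or Cox models, and the rate-based and time-to-event options need a risk window that matches the deaths counted.

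For UTCI, a single series for the whole catchment is the same for both arms, so it contains no treatment contrast to estimate.

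For hospital use, admissions alone and admissions plus visits are different counts. Leaving both in the plan allows a choice after the data have been seen, which is easy to avoid.

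**Working it through.** The plan gives no figure of its own to reproduce here. The check is a day count for mortality and a comparison of the tables with the analysis text for the other two outcomes.

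**Mortality**

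- Study period, from the Study design section: 365 + 365 = 730 days.
- Peak summers is not defined for surveillance. The article offers three candidate seasons: April to June (the Sessions calendar, summer), May to August (Study setting, hottest period) and April to October (Sessions calendar, summer plus late summer).
- Covered days = days in the season × 2 years. Uncovered share = 1 − covered days / 730.

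| Reading | Days per year | Covered days | Covered | Uncovered |
|---|---|---|---|---|
| April–June | 91 | 182 | 24.9% | 75.1% |
| May–August | 123 | 246 | 33.7% | 66.3% |
| April–October | 214 | 428 | 58.6% | 41.4% |

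These are shares of time. They become shares of deaths only if deaths are spread evenly over the year, which is an assumption. Under it, and ignoring between-cluster variation, the standard error of a log rate ratio relative to full ascertainment grows by √(730 / covered days): √(730/182) = 2.00, √(730/246) = 1.72 and √(730/428) = 1.31. If deaths concentrate in the hot months, fewer are missed and the loss is smaller.

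**UTCI**

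- *Table 3 unit taken literally.* Every cluster carries the same value at each time. The mean in one arm minus the mean in the other is the same series subtracted from itself, so nothing can be estimated about ReHAB.
- *Table 2 placement.* One Drop D2 per cluster gives 22 outdoor series, 11 per arm.
- *Components.* Table 1 lists four for UTCI: air temperature, humidity, wind speed and radiant temperature. The Environmental data collection section assigns outdoor temperature and humidity to the Drop and HOBO devices. Daily wind and solar radiation come from local weather station data. Table 2 also has the Kestrel 5400 recording wind and radiation, but it is rotated.
- *Result.* Two of the four components are cluster-specific. With station data, the other two are common to both arms. With a meter moved between clusters, they depend on when it stood in each one. If those dates differ between arms in season or weather, part of an arm difference in UTCI is a difference in dates.

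**Hospital use**

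The row label names both visits and hospitalisations in both tables. The Table 1 definition counts admissions only; the Table 3 detail counts admissions or visits. The analysis text follows the broader wording.

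**The case against.** A reader might infer more than the documents support, in four ways.

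- *That the UTCI comparison cannot be done.* Table 3 lists the Drop D2 among the UTCI devices and Table 2 puts one in each cluster. A model with cluster random intercepts can therefore be fitted. Table 2 might even mean one Kestrel 5400 per cluster, moved between spots within it, which would give local wind and radiation. The article does not say. This answer stands against impossibility, but it leaves the Table 3 unit wrong and the wind and radiation source open.
- *That the true UTCI effect must be zero.* ReHAB includes enhanced shading and communal outdoor shelters, and the Structural modification section gives the community interventions a role for outdoor workers. The effect at a logger may be small, but nothing in the documents makes it zero.
- *That two thirds of deaths will be lost.* This needs both the May to August reading and an even spread of deaths. Neither is stated.
- *That the mortality comparison is biased.* Table 3 sets the same schedule for both arms. Rates would be understated only if summer deaths were divided by year-round person-time, and no section says that; the primary analysis uses person-weeks at risk.

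It can also be said that the baseline, periodic and endline surveys planned for all 22 clusters include a household-members section and could pick up off-season deaths. They could, but the Household data collection section lists what they collect and does not mention deaths. The hospital mismatch is fairly called minor, since only the Table 1 definition omits visits.

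**Conclusion.** The three inconsistencies are real and should be reconciled. All concern secondary outcomes; neither co-primary outcome nor its sample size or model is touched.

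Mortality matters most. Followed as written, the schedule does not yield the outcome that Table 1 defines: 41% to 75% of the study period has no scheduled death ascertainment, or 66% if peak summers means May to August. The range rests on the three seasonal readings above. The consequences are fewer deaths, lower precision and a changed estimand; a biased arm ratio is not shown.

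For UTCI, the stated unit gives no arm contrast. Using the per-cluster loggers, the contrast is estimable but only partly cluster-specific unless wind and radiation are measured locally, and it could reflect the timing of a rotated meter.

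For hospital use, one outcome has two definitions, and the size of the difference cannot be judged from the article.

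**What to change.** 1. **Mortality.** Define peak summers by calendar dates. Then choose one of two routes:
   - rename the outcome peak-summer mortality and limit person-time to the surveillance weeks; or
   - keep the study-period definition and add a vital-status question, with date of death, against the household roster at the April, July, December and endline visits already planned.

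   The first costs only wording. The second costs one short item per visit and is best added early, because off-season deaths are harder to establish later.
2. **UTCI.** Choose one of two routes:
   - compute it per cluster, correct the unit in Table 3, state the source of wind and radiation, and balance any meter rotation over time between arms; or
   - drop it as an arm-compared outcome and report the shared-station catchment series as ambient context or use it as an ambient covariate.

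   Do not adjust for a per-cluster UTCI: shading or shelters could affect it, so it is a post-randomisation variable. The cost is wording, plus a rotation schedule on the first route.
3. **Hospital use.** Put one definition, admissions only or admissions plus visits, in Table 1, Table 3 and the secondary analysis section. The cost is wording.

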**Methods and analysis:**

This trial aims to evaluate the effectiveness of a comprehensive Resilience and Heat Adaptation Bundle (ReHAB) that integrates behavioural and structural interventions to reduce heat-related morbidity and mortality and improve internal ambient conditions in rural settings of Pakistan. This study is a prospective, cluster-randomised trial, comprising 22 clusters allocated to intervention and control arms in a 1:1 ratio. The ReHAB intervention combines community education and awareness with targeted structural improvements, including roof and wall treatments, enhanced shading, improved ventilation, sustainable energy installations and communal outdoor shelters. Health and behavioural data will be collected through household surveys, while wearable devices and environmental sensors will measure individual heat exposure and record indoor and outdoor thermal conditions.

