##### Community education and awareness

The educational component of ReHAB was developed based on findings from the formative phase, including systematic review, qualitative work, stakeholder consultations and pilot testing. Community mobilisation will be implemented throughout the intervention. Community groups (CGs) will be established across all 11 intervention clusters, with separate male and female representation. Each CG (6–8 members) will include local government representatives, elders, religious leaders and male and female community members. CGs will lead mobilisation activities and support surveillance of the primary outcome (heat illness).

Activities will include dissemination of heatwave warnings, awareness sessions and door-to-door outreach on heat-health practices (hydration, clothing and activity scheduling). CGs will maintain logbooks to record healthcare visits within their catchment areas and attendance in community meetings. Practical demonstrations of cooling strategies (eg, shade setup, light clothing, wet towels, misting and work–rest–shade cycles) will be conducted, supported by Information, Education and Communication (IEC) materials. This structured, behaviour-focused delivery aims to ensure both the uptake and sustainability of protective cooling practices. Community hydration measures (eg, temporary drinking water facilities) will also be implemented to reduce dehydration among outdoor workers.

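### The personal heat-exposure model adjusts for follow-up activity and illness, so its arm coefficient is not the total intention-to-treat effect

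*Protocol article*

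**What the plan says.** The last paragraph of Secondary outcome analysis treats personalised heat exposure as a continuous longitudinal outcome in a linear mixed model "incorporating time-varying covariates such as occupation, daily activity patterns and reported illness history". It closes with: "All analyses will report adjusted mean differences with corresponding 95% CIs". It gives no version of this model without those covariates, and it does not call the model a mediation or direct-effect analysis.

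Table 1 (Outcomes) gives the outcome as: "Defined as mean daily external temperature each individual experiences (indoors and outdoors) as recorded by a wearable temperature monitor".

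Table 3 lists the survey content for this outcome as "Occupation, sun exposure, illness history, daily routine", at baseline and monthly. The sentence introducing the table says: "Monthly data will be collected from the subset population to provide detailed insights into heat stress and intervention effectiveness".

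Community education and awareness includes "door-to-door outreach on heat-health practices (hydration, clothing and activity scheduling") among its activities, and adds: "Practical demonstrations of cooling strategies (eg, shade setup, light clothing, wet towels, misting and work–rest–shade cycles) will be conducted".

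Statistical analysis applies intention to treat to all analyses. Its general adjustment rule names relevant baseline covariates and baseline values of the outcome.

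**The concern.** In a randomised comparison, the total effect of assignment is estimated without conditioning on variables that assignment can change. Here the outcome is the temperature a person meets indoors and outdoors, so it depends on where that person is and when. The bundle teaches people to change exactly that. Holding follow-up activity fixed asks how the arms would differ if their activity were the same, which is a different question from what ReHAB does to personal exposure. Illness reported during follow-up raises a second difficulty, because it may result from exposure.

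At stake is the reading of an outcome that covers both settings in which people meet heat. If the education component works partly by moving activity out of the heat, the planned coefficient would not credit it with that part.

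**Working it through.** The protocol states no effect size, sample size or power for personalised heat exposure, so there is no figure to reproduce. The check sets the passages side by side and then illustrates the mechanism.

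**1. Timing.** The analysis text calls the covariates time-varying, and Table 3 collects the same items at baseline and every month. Reading them as fixed baseline history fits neither place.

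**2. Place on the causal path.** Activity scheduling and work–rest cycles are taught in the intervention arm only. Activity determines location and time of day, and these determine the temperature recorded. Follow-up activity is therefore a mediator by design. Illness in follow-up is plausibly downstream of exposure. Nothing in the document suggests that the bundle changes occupation.

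**3. Consistency.** Statistical analysis sets a baseline-covariate rule under intention to treat. The subset paragraph departs from it for this outcome without giving a reason. The result is not a clean direct effect either, because common causes of activity (or illness) and exposure are left open.

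**4. Formula, with assumed inputs.** Let T be the total effect, s the share running through activity, and r the reliability of the activity measure given arm. In a linear model with non-differential error and no unmeasured mediator–outcome confounding:

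adjusted coefficient = T × (1 − s × r)

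With T = -1.0 °C:
- s = 0: -1.0 × (1 − 0) = -1.0
- s = 0.25, r = 1: -1.0 × (1 − 0.25) = -0.75
- s = 0.50, r = 1: -0.50
- s = 0.75, r = 1: -0.25
- s = 0.25, r = 0.5: -1.0 × (1 − 0.125) = -0.875
- s = -0.25, r = 1 (activity change raises exposure, for example if cooler conditions lead to longer outdoor work): -1.0 × (1 + 0.25) = -1.25

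**5. Simulation, with assumed inputs.** There were 11 clusters per arm, 8 adults per cluster and 12 monthly records, with a true total effect of -1.0 °C. Outdoor time fell by 1 hour under intervention (SD 1.5), and the log-odds of illness rose by 0.5 per °C. Arm coefficients are averaged over 200 runs. They come from least squares, not the planned mixed model, so they show the mechanism and not an expected size.

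| Share through activity | No follow-up covariates | Activity | Illness | Both |
|---|---|---|---|---|
| 0 | -0.993 | -0.992 | -0.956 | -0.955 |
| 0.10 | -0.990 | -0.889 | -0.952 | -0.855 |
| 0.25 | -1.009 | -0.756 | -0.966 | -0.726 |
| 0.50 | -0.991 | -0.496 | -0.942 | -0.478 |
| 0.75 | -1.002 | -0.251 | -0.934 | -0.241 |

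Without the follow-up covariates the total effect is recovered in every row. Adjusting for activity removes about the mediated share. Illness alone removes between 1 − 0.956/0.993 = 3.7% and 1 − 0.934/1.002 = 6.8%, but only under the simulated illness mechanism.

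**The case against.** The best defence is that the covariate list is illustrative, that exact covariates and any unadjusted companion model belong in a statistical analysis plan that is not shown, and that time-varying covariates can sharpen a noisy repeated measure. In the same paragraph, the explicit aim of estimating intervention effects is attached to the physiological markers. This does not rescue the text. An illustrative list still fixes the kind of covariate, and the closing sentence makes adjusted mean differences the reported result for all subset analyses. Season and outdoor temperature can serve precision without being changed by assignment.

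Other parts of the defence stand, and they limit the point:
- **Rank of the outcome.** Personalised heat exposure is a subset outcome. It is not named in the objectives, has no sample size of its own and lies outside the fixed-sequence test, so its model is not confirmatory.
- **Extent.** A reader might infer that the whole behavioural component is adjusted away. Only what the activity items capture is removed. Shade, misting and heat warnings need not pass through those items, and structural cooling need not act through activity.
- **Direction.** A reader might infer bias towards no effect. That holds only if activity change lowers exposure.
- **Illness.** The trial aims "to reduce heat-related morbidity and mortality and improve internal ambient conditions in rural settings of Pakistan", which invites the reading that the illness covariate is the co-primary outcome. The document does not say so. Heat-related illness comes from a separate weekly system, and the covariate comes from the personal-exposure survey. Any collider bias is therefore conditional on what that item records.

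**Conclusion.** The point holds for one subset outcome. As written, the personal heat-exposure model conditions on follow-up activity, which the bundle is designed to change, and on follow-up illness, which may follow from exposure. Its arm coefficient is therefore not the total intention-to-treat effect, and it departs from the protocol's own baseline-covariate rule. This conclusion rests on the text alone.

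The size cannot be derived from the documents. The coefficient loses the share of the effect that runs through activity as measured, and that share could be nil, small or large. The figures in °C above rest on an assumed -1.0 °C effect and assumed shares, and must not be read as estimates for this trial. The direction of bias through illness or unmeasured confounding is also undetermined. The analyses of heat-related illness and quality of life are not touched.

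**What to change.** Replace the covariate clause for personalised heat exposure with a main model containing arm, month or season, ambient outdoor temperature, baseline exposure and baseline covariates only, including baseline occupation. Outdoor temperature is best taken from the central or local weather station, which the intervention cannot change. State that any model containing follow-up activity or illness is a separately labelled exploratory mediation analysis, with its assumptions given.

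The cost is about one sentence in the protocol or analysis plan. No new data are needed: Table 3 already schedules this outcome and its survey at baseline, and outdoor temperature is already recorded. The change should be made before outcome data are analysed, so that the choice of model cannot depend on the results.
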